### **6.3 Time of procedure:**

Estimated date of first subject enrolled: January 2016

Estimated date of last subject enrolled: April 2017

Estimated date of last subject completed: May 2019

Estimated date of study report finalized: December 2019

**TABLE 1. STUDY PLAN FLOW TABLE**

| Visit                                         | 1          | 2             | 3            | 4          | 5          | 6     | 7     | 8          | 9     | 10    | 11         | 12    | 13    | 14         | 15    | 16    | 17    | 18    | 19    | 20         | 21    | 22    | 23    | 24    | 25    | 26         | 1 |
|-----------------------------------------------|------------|---------------|--------------|------------|------------|-------|-------|------------|-------|-------|------------|-------|-------|------------|-------|-------|-------|-------|-------|------------|-------|-------|-------|-------|-------|------------|---|
| Week                                          | -6         | 0             | 4            | 8          | 12         | 6     | 0     | 26         | 0     | 4     | 38         | 42    | 6     | 52         | 6     | 0     | 4     | 8     | 2     | 78         | 2     | 6     | 0     | 4     | 8     | 104        |   |
| Window (week)                                 |            | 0             | ±1           | ±1         | ±1         | ±1    | ±1    | ±1         | ±1    | ±1    | ±1         | ±1    | ±1    | ±1         | ±1    | ±1    | ±1    | ±1    | ±1    | ±1         | ±1    | ±1    | ±1    | ±1    | ±1    | ±1         |   |
| Study period                                  | Screening  | Randomization | Intervention |            |            |       |       |            |       |       |            |       |       |            |       |       |       |       |       |            |       |       |       |       |       |            |   |
| Follow-up mode                                | outpatient | outpatient    | outpatient   | outpatient | outpatient | phone | phone | outpatient | phone | phone | outpatient | phone | phone | outpatient | phone | phone | phone | phone | phone | outpatient | phone | phone | phone | phone | phone | outpatient |   |
| Written informed consent                      | X          |               |              |            |            |       |       |            |       |       |            |       |       |            |       |       |       |       |       |            |       |       |       |       |       |            |   |
| Inclusion/Exclusion criteria                  |            | X             |              |            |            |       |       |            |       |       |            |       |       |            |       |       |       |       |       |            |       |       |       |       |       |            |   |
| Discontinue or not                            |            |               | X            | X          | X          | X     | X     | X          | X     | X     | X          | X     | X     | X          | X     | X     | X     | X     | X     | X          | X     | X     | X     | X     | X     | X          | X |
| Medical history                               | X          |               |              |            |            |       |       |            |       |       |            |       |       |            |       |       |       |       |       |            |       |       |       |       |       |            |   |
| Physical examination                          | X          | X             | X            | X          | X          |       |       | X          |       |       | X          |       |       | X          |       |       |       |       |       | X          |       |       |       |       |       |            | X |
| Distribution/collectio                        | X          | X             | X            | X          | X          |       |       | X          |       |       | X          |       |       | X          |       |       |       |       |       | X          |       |       |       |       |       |            | X |
| n of patient log                              |            |               |              |            |            |       |       |            |       |       |            |       |       |            |       |       |       |       |       |            |       |       |       |       |       |            |   |
| Adjustment of basic medication    | X          | X             | X            | X          | X          | X     | X     | X          | X     | X     | X          | X     | X     | X          | X     | X     | X     | X     | X     | X          | X     | X     | X     | X     | X     | X          | X |
| Counting/retrieval of medication  |            |               |              | X          | X          |       |       | X          |       |       | X          |       |       | X          |       |       |       |       |       | X          |       |       |       |       |       |            | X |
| Distribution of medication        |            | X             | X            | X          | X          |       |       | X          |       |       | X          |       |       | X          |       |       |       |       |       | X          |       |       |       |       |       |            |   |
| Past/concomitant medications                  | X          | X             | X            | X          | X          | X     | X     | X          | X     | X     | X          | X     | X     | X          | X     | X     | X     | X     | X     | X          | X     | X     | X     | X     | X     | X          | X |
| Compliance evaluation                         |            | X             | X            | X          | X          |       |       | X          |       |       | X          |       |       | X          |       |       |       |       |       | X          |       |       |       |       |       |            | X |

### Efficacy evaluation

|                                             |   |   |   |   |   |   |   |   |   |   |   |   |   |   |   |   |   |   |   |   |
|---------------------------------------------|---|---|---|---|---|---|---|---|---|---|---|---|---|---|---|---|---|---|---|---|
| (0,60,120min)                               |   |   |   |   |   |   |   |   |   |   |   |   |   |   |   |   |   |   |   |   |
| C-peptide*                                  | * |   |   |   |   |   |   | * |   |   |   | * |   |   |   |   | * |   |   | * |
| (0,60,120min)                               |   |   |   |   |   |   |   |   |   |   |   |   |   |   |   |   |   |   |   |   |
| Blood glucose                               | X |   |   |   |   |   |   | X |   |   |   | X |   |   |   |   | X |   |   | X |
| HbA1c                                       | X |   |   |   | X |   |   | X |   |   |   | X |   |   |   |   | X |   |   | X |
| Blood glucose self monitoring and recording | X | X | X | X | X | X | X | X | X | X | X | X | X | X | X | X | X | X | X | X |
| Safety Assessment                    |   |   |   |   |   |   |   |   |   |   |   |   |   |   |   |   |   |   |   |   |
| 25(OH)D*                                    | * |   | * |   | * |   |   | * |   |   |   | * |   |   |   |   | * |   |   | * |
| Blood routine                               | X |   | X |   | X |   |   | X |   |   |   | X |   |   |   |   | X |   |   | X |
| Blood biochemical test          | X |   | X |   | X |   |   | X |   |   |   | X |   |   |   |   | X |   |   | X |
| Blood electrolyte                           | X |   | X |   | X |   |   | X |   |   |   | X |   |   |   |   | X |   |   | X |
| Urine pregnancy test            | X |   | X |   | X |   |   | X |   |   |   | X |   |   |   |   | X |   |   | X |
| 24-hour urine calcium and phosphate         | X |   | X |   | X |   |   | X |   |   |   | X |   |   |   |   | X |   |   | X |
| 12-lead ECG                                 | X |   |   |   |   |   |   | X |   |   |   | X |   |   |   |   | X |   |   | X |
| Urinary system BUS                          | X |   | X |   | X |   |   | X |   |   |   | X |   |   |   |   | X |   |   | X |
| Adverse event                               |   | X | X | X | X | X | X | X | X | X | X | X | X | X | X | X | X | X | X | X |
| Other Assessment                     |   |   |   |   |   |   |   |   |   |   |   |   |   |   |   |   |   |   |   |   |
| GADA*                                       | * |   |   |   |   |   |   |   |   |   |   | * |   |   |   |   |   |   |   | * |
| Gene analysis*                              | * |   | * |   | * |   |   | * |   |   |   | * |   |   |   |   | * |   |   | * |
| Complications                   | X |   |   |   |   |   |   |   |   |   |   | X |   |   |   |   |   |   |   | X |

\*, Centralized test; 1.The contents of the discontinuation visit are consistent with that of visit 26; 2. Metformin (and insulin); 3. Saxagliptin/VitD3 (Group A does not involve any dispensation, check or retrieval of investigational medication; 4.Blood biochemical test include: Lipid (TC, LDL-C, HDL-C, and TG), liver function (AST, ALT, TBIL, DBIL, and ALB), renal function (BUN, Cr, andUA); 5.Apply to women at child-bearing period; 6.Tests for complications include: ① macroangiopathy: 1) Color Doppler Ultrasound of carotid artery, vertebral artery, and lower extremities arteries, 2) ECG; ② microangiopathy: 1) retinopathy: fundus examination and photography, 2) diabetic nephropathy: a.UACR, b. calculate eGFR; ③ peripheral neuropathy: 1) electroneuromyography, 2) physical examination using the tools in the diabetic neuropathy screening kit; ④ osteoporosis: bone mineral density. (Will accept Color Doppler Ultrasound of artery, fundus examination and photography, and electroneuromyography results from Grade A Tertiary Hospitals within 6 months prior to screening; will accept BMD test results from Grade A Tertiary Hospitals within 12 months of randomization).

## **6.4 Visiting time**

### **Screening**

#### **6.4.1 Visit 1 (Week -6 - Week 0) 【outpatient visit】**

- Sign written informed consent.
- Medical history
- Physical examination
- Distribution of patient diary and glucose meter
- Initiation or adjustment of basic medication
- Record of past/ concomitant medication (record medication used within 6 months before the screening date)
- MMTT test 0, 60, 120 min blood glucose (conduct at each study site); 0, 60, 120 min C-peptide (deliver to the central laboratory)
- GADA, 25(OH)D test, gene analysis (deliver to the central laboratory)
- HbA1C, blood routine test, blood biochemical, blood electrolyte, urine pregnancy test, 24-hour urine calcium and phosphate
- 12-ECG
- BUS of urinary system
- Tests for complications

### **Randomization**

#### **6.4.2 Visit 2 (Week 0) 【outpatient visit】**

- Verify inclusion/exclusion criteria
- Physical examination

- Collection/distribution of patient diary
- Adjustment of basic medication
- Dispensation of investigational medication
- Record past/ concomitant comitant medication
- Evaluate compliance by the investigator according to the subject's basic medication and self-monitored blood glucose level
- Record adverse events

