### Study design

This is a multi-center, open-label, 1:1:1 randomized controlled trial, compromised of a 6-week run-in period and the 104-week treatment period.

---

Target population: LADA patients signed an informed consent ( the definition of LADA subjects please refer to the inclusion standards of the study) ; aged 18-70 years old; duration should be less than 4 years.

Randomize all subjects who meet all eligibility criteria and do not meet any of the exclusion criteria into three groups by a central dynamic random method: metformin (and insulin) , metformin (and insulin) + saxagliptin , metformin (and insulin) + saxagliptin + vitamin D3.

The main purpose of this study: evaluate whether saxagliptin (and vitamin D3) as add-on therapy to metformin (and insulin) can better protect islet beta cell function than metformin (and insulin).

Safety objective: Adverse events, serious adverse events, blood glucose, blood routine, serum creatinine, serum calcium and 25 (OH) D monitoring.

---

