#### **Exclusion criteria:**

- 1) Women who are pregnant, intending to become pregnant during the study period, or currently lactating females;
- 2) Gestational diabetes mellitus or other specific types of diabetes;
- 3) Allergy to saxagliptin, vitamin D3 and excipient;
- 4) Treated with medications including DDP-IV inhibitors, GLP-1 analogues, GLP-1 receptor agonists, and TZDs in the past 8 weeks prior to randomization;
- 5) Patients with hypercalcemia (exceeding the upper limit of the reference range )

- 6) Treatment with systemic corticosteroids therapy (oral or intravenous) consecutively for over 7 days in the past 6 months;
- 7) ALT or AST more than 3 times of the normal upper limit, TBIL more than 2 times of the normal upper limit;
- 8) Serum creatinine levels  $\geq 1.5$  mg/dL for males and  $\geq 1.4$ mg/dL for females or CrCl  $\leq 50$  mL/min;
- 9) Patients with malignant tumors;
- 10) Patients with mental disorders;
- 11) History of alcohol abuse or illegal drug abuse;
- 12) Serious systemic disease not suitable for the study by evaluation of the investigator.

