## **8.9 Pregnancy**

Before signing the informed consent, investigators should notify childbearing age participants of the importance of contraception throughout the study and the potential risks of accidental pregnancy. The subject must sign the informed consent to claim that the investigator has discussed the risk factors and outcomes with her.

If a subject becomes pregnant during the course of the study, investigational product should be discontinued immediately and the procedure of study discontinuation of the subject should be finished. Pregnancy itself is not regarded as an adverse event unless there is a suspicion that the investigational product under study may have interfered with the effectiveness of a contraceptive medication. Congenital abnormalities/birth defects and spontaneous miscarriages should be reported and handled as SAEs. Elective abortions without complications should not be handled as AEs. The outcome of all pregnancies (spontaneous miscarriage, elective termination, ectopic pregnancy, normal birth or congenital abnormality) should be followed up and documented even even the subject was discontinued from the study.

If any pregnancy occurs in the course of the study, then investigators or other site personnel inform sponsor within one day.

The same timelines apply when outcome information is available.

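### Pregnancy is an absolute exclusion, but no pregnancy test is scheduled at Visit 2, so a woman can be randomised on a result up to 6 weeks old

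*Protocol*

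**What the plan says.** Exclusion criterion 1 in section 4.1 bars "Women who are pregnant, intending to become pregnant during the study period, or currently lactating females". Section 4.4 makes eligibility absolute: a subject who fails the criteria is not to be enrolled or given study medication, and no exception is allowed.

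The synopsis describes a "6-week run-in period and the 104-week treatment period". Section 6.4.1 places the screening visit, "Visit 1 (Week -6 - Week 0"), at the start of or within that run-in, and its laboratory list includes "blood electrolyte, urine pregnancy test". A footnote limits the test to women of child-bearing age.

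Section 6.4.2 lists eight procedures for Visit 2 at week 0. Among them are "Verify inclusion/exclusion criteria" and "Dispensation of investigational medication"; a pregnancy test is not. In Table 1 the eligibility row is marked at Visit 2 only, and the urine pregnancy row is blank there. Section 6.4.3 schedules the next test at Visit 3, week 4 ±1.

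Section 8.9 provides for counselling on contraception before consent. If pregnancy occurs on study, it says that "investigational product should be discontinued immediately and the procedure of study discontinuation of the subject should be finished".

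**The concern.** Pregnancy status can change at any time during a run-in designed to last 6 weeks. The protocol has an absolute rule and a visit at which the rule is to be checked, but it schedules no current measurement for that check. A site that performs every listed procedure, and nothing more, can record a woman as eligible on a test done when she entered screening.

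What is at stake is exposure of a woman the protocol says must not receive study drug. Had the pregnancy been found at Visit 2, she would have been a screen failure. Found at Visit 3, she is a randomised subject to whom section 8.9 applies, and under section 6.5 she is not replaced.

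**Working it through.** The protocol states no figure for this gap, so there is none to reproduce. The check sets the visit lists beside Table 1 and then does interval arithmetic on the visit windows.

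**Do the two sources agree?**

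| Visit | Week | Pregnancy test in 6.4 | Pregnancy test in Table 1 | Eligibility verified | Drug dispensed |
|---|---|---|---|---|---|
| 1 | -6 to 0 | yes | marked | no | no |
| 2 | 0 | no | blank | yes | yes |
| 3 | 4 ±1 | yes | marked | no | yes |

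The visit lists and the table agree at all three visits, so the absence at Visit 2 is not an artefact of how the table was extracted. No other section calls for a repeat test before randomisation. Section 8.9 covers counselling and what happens once a pregnancy is known.

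**Inputs**
- Visit 1 falls between week -6 and week 0 (section 6.4.1).
- Visit 2 is at week 0 with a window of 0 (Table 1).
- Visit 3 is at week 4 ±1, that is weeks 3 to 5 (section 6.4.3).
- Saxagliptin is taken from randomisation and vitamin D3 after it (section 5.2).
- Group A receives no investigational drug (Table 1, footnote 3).

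**Intervals**
- Age of the test at randomisation = week 0 minus the week of Visit 1: from 0 - 0 = 0 weeks to 0 - (-6) = 6 weeks.
- Time on study drug before the next scheduled test = week of Visit 3 minus week 0: 4 - 1 = 3 weeks to 4 + 1 = 5 weeks.
- Gap between the two scheduled tests that span the first dose: shortest 0 + 3 = 3 weeks; longest 6 + 5 = 11 weeks, or 6 + 4 = 10 weeks if Visit 3 is on its nominal date.

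Six weeks is a maximum, but the synopsis makes the run-in a planned 6-week period. A gap near that length therefore follows from the design and is not a scheduling slip.

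**Effect on the primary analysis**

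Section 9.2 needs 76 subjects per group; 76 / (1 - 0.20) = 95, set to 100. Each arm can therefore lose 100 - 76 = 24 subjects before falling below the calculated number. One pregnancy is 1/100 = 1% of an arm. The discontinuation visit repeats Visit 26, including the meal-test C-peptide (sections 6.4.15 and 6.6), so a post-baseline value is planned. The primary model is a mixed model for repeated measures (section 9.4.1). In the sensitivity analysis that carries the last observation forward, such an early value would stand in for week 104, but only for a handful of subjects at most.

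**The case against.** The strongest reply is that the schedule permits this outcome but does not produce it. At Visit 2 the investigator verifies every criterion and examines the patient, and nothing forbids asking about a missed period or repeating the test. Women intending pregnancy are already excluded, contraception is discussed before consent, and section 6.1 lets subjects attend outside the schedule for safety reasons. All of this stands. It makes cases fewer, but it requires no test, and 20 to 45 centres may each act differently.

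A second reply is that the exclusion, section 6.4 and Table 1 do not contradict one another, and that other laboratory exclusions (calcium, liver enzymes, creatinine) also rest on Visit 1 without a repeat. That is correct: the protocol screens once and verifies later, and this is a weak point of design, not a misstatement. Pregnancy is still the case where a negative result says least about status weeks later, because it is a state that can begin on any day.

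A third reply is that later gaps between tests are longer, for example from week 52 to week 78. Those gaps concern pregnancy arising on study, which section 8.9 manages. This one concerns eligibility before first exposure.

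Readers might infer more than the documents support:
- *Any woman who conceives in the run-in will be randomised, dosed and found only at week 4.* The text supports only that she can be, and that no scheduled test would find her earlier.
- *Every such woman is exposed to study drug.* Only two of the three arms receive it.
- *She must leave the study.* Section 6.6 says pregnant subjects may be discontinued; section 8.9 says the discontinuation procedure should be completed.
- *The trial's power or primary comparison is at risk.* Sample size already allows for about 20% drop-out, and nothing in the documents suggests a bias between arms.

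**Conclusion.** The point holds as a safety and eligibility gap of low frequency. Pregnancy status at randomisation can rest on a scheduled test up to 6 weeks old, and in the two saxagliptin arms study drug can be taken for 3 to 5 weeks before the next scheduled test. The effect on the primary analysis is negligible and is no part of the case.

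The conclusion rests on the following:
- Dosing begins at week 0, as section 5.2 indicates.
- Sites carry out the listed procedures without adding unscheduled tests.
- A very early pregnancy can give a negative urine test. This is an assumption that the documents do not address. The part of the argument about conception during the run-in does not depend on it.

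The number of cases cannot be derived from the documents. It is limited to women of child-bearing age in a population aged 18 to 70, and is expected to be small.

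**What to change.** Reconcile exclusion criterion 1, the Visit 2 eligibility check and the test schedule. In Table 1 and section 6.4.2, add a urine pregnancy test at Visit 2 for women of child-bearing age, and state that the result is to be seen before randomisation and dispensing. Apply it in all three arms so that eligibility is judged alike before allocation is known.

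Keep the Visit 1 test. Moving it to Visit 2 would leave the run-in without any pregnancy test, although basic medication is started or adjusted and the first meal test is done at Visit 1.

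The cost is one mark in Table 1, one line in section 6.4.2, and one urine strip per woman of child-bearing age at a visit she already attends. A very recent conception could still be missed at Visit 2, so the change shortens the gap without closing it entirely.

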## **Intervention**

### **6.4.3 Visit 3 (Week 4 $\pm$ 1week) 【outpatient visit】**

- Check for discontinuation of the study
- Physical examination
- Collection/distribution of patient diary
- Adjustment of basic medication
- Counting/retrieval of investigational medication
- Dispensation of investigational medication
- Record past/ concomitant medication
- Evaluation of compliance
- 25(OH)D test, gene analysis (deliver to the central laboratory)
- blood routine test, blood biochemical, blood electrolyte, urine pregnancy test, 24-hour urine calcium and phosphate
- BUS of urinary system

- Record adverse events

#### **6.4.4 Visit 4 (Week 8 $\pm$ 1week) 【outpatient visit】**

- Check for discontinuation of the study
- Physical examination
- Collection/distribution of patient diary
- Adjustment of basic medication
- Counting/retrieval of investigational medication
- Dispensation of investigational medication
- Record past/ concomitant medication
- Evaluation of compliance
- Record adverse events

#### **6.4.5 Visit 5 (Week 12 $\pm$ 1week) 【outpatient visit】**

- Check for discontinuation of the study
- Physical examination
- Collection/distribution of patient diary
- Adjustment of basic medication
- Counting/retrieval of investigational medication
- Dispensation of investigational medication
- Record past/ concomitant medication
- Evaluation of compliance
- 25(OH)D test, gene analysis (deliver to the central laboratory)

- HbA1c, blood routine test, blood biochemical, blood electrolyte, urine pregnancy test, 24-hour urine calcium and phosphate
- BUS of urinary system
- Record adverse events

